## Abstract

**Background:**

Rehabilitation is beneficial for individuals with cancer across all phases of care, but access remains limited for many survivors, including individuals with melanoma. As new treatment strategies for melanoma are introduced, there is an opportunity to assess perioperative rehabilitation strategies for patients undergoing surgery during and after neoadjuvant treatment.

**Objective:**

This paper describes the protocol for a 2-armed pilot randomized controlled trial with the overall objective of determining the feasibility and preliminary effects of a perioperative rehabilitation strategy for individuals with melanoma at a single cancer institution in Ontario, Canada.

**Methods:**

In total, 30 participants, including English-speaking adults with a current melanoma diagnosis scheduled to undergo surgery after neoadjuvant immunotherapy, will be randomized 1:1 to either the intervention or control group. The intervention will include 4 perioperative intervention sessions (2 sessions before surgery and 2 sessions after surgery) led by a trained physiotherapist or kinesiologist. Participants in the intervention group will receive education on the benefits of exercise; how to exercise safely; and rehabilitation techniques to maximize range of motion, strength, and function. Participants will also receive a tailored exercise program and will establish goals and action plans at each session. The control group will receive usual care (no rehabilitation). The primary outcome is feasibility (measured via recruitment, retention, and adherence rates). Secondary outcomes will be collected before and after the intervention and include overall impairment score (measured via the Edmonton Symptom Assessment Scale), physical activity level (Godin Leisure Time Exercise Questionnaire), functional mobility (6-minute walk test and 30-second sit-to-stand test), range of motion (goniometry), grip strength (handheld dynamometry), quality of life (Functional Assessment of Cancer Therapy-Melanoma), perception of health status (EQ-5D-3L), and medication use. Feasibility will be analyzed using descriptive statistics (mean [SDs] or frequency [%]), as appropriate. Secondary outcomes will be reported using means, SD, and CIs of outcomes. Cohen *d* effect sizes will be calculated and reported for each secondary outcome to inform a future full-scale trial. STATA/MP (version 14) will be used for all statistical analysis, with significance set at *P*<.05.

**Results:**

Trial enrollment began in June 2026, and 3 participants have been recruited to date. Recruitment is expected to be completed by December 2026. Results will be submitted for publication by mid or late 2027.

**Conclusions:**

This pilot trial aims to address the evidence gap on the feasibility and preliminary effects of rehabilitation for individuals with melanoma, laying the groundwork for a larger randomized controlled trial and future implementation of rehabilitation for this population. By implementing rehabilitation around the surgical phase, we aspire to enhance patient outcomes by maximizing function and reducing side effects, facilitating a faster return to meaningful daily activities.

**Trial Registration:**

ClinicalTrials.gov NCT07320222; https://clinicaltrials.gov/study/NCT07320222

**International Registered Report Identifier (IRRID):**

PRR1-10.2196/90946

## Introduction

### Background

Melanoma, a serious form of skin cancer, has become increasingly prevalent in Canada [1]. In recent years, Canadians have become increasingly aware of the importance of early detection and treatment [1]. However, surgical intervention for melanoma, while often necessary for effective management, can result in significant physical and emotional challenges for patients [2,3]. In Canada, the treatment landscape for melanoma is evolving with the introduction of new neoadjuvant immunotherapy regimens aimed at improving patient outcomes for those with more advanced melanoma [4,5]. Recent advancements include the use of combination therapies that integrate immune checkpoint inhibitors with targeted therapies, which are designed to enhance tumor response before surgical resection [4]. These innovative approaches aim to reduce tumor size and potentially improve the rate of complete surgical removal [4]. Ongoing clinical trials continue to evaluate the effectiveness and safety of these regimens, reflecting a commitment to optimizing preoperative treatment strategies and improving outcomes for those with melanoma [6]. Neoadjuvant immunotherapy is commonly administered over 6 weeks after the initial consultation for ipilimumab-nivolumab combination therapy or over 12 weeks after the initial consultation for pembrolizumab monotherapy. While these advances offer promising improvements in disease management, the introduction of immunotherapy during the preoperative period may also increase treatment burden. Patients may experience the combined effects of surgery and immunotherapy-related toxicities, including fatigue, reduced muscle strength, and impaired physical function. These potential consequences should be considered and proactively addressed alongside these changes in medical management.

Rehabilitation plays a crucial role in the recovery process for individuals with cancer, helping individuals regain strength, range of motion (ROM), mobility, and confidence [7-9]. Comprehensive rehabilitation programs can support not only physical healing but also address psychological concerns, enabling patients to better navigate their journey toward recovery and improved quality of life [7-10]. Exercise is one component of rehabilitation and has demonstrated improvements in fitness levels, strength, physical function, fatigue, and quality of life in those with cancer [7,8,10]. Current exercise guidelines for those with cancer include weekly aerobic, resistance, and flexibility training [7,11]. Aerobic exercise can help improve cardiovascular fitness, while resistance and functional exercise support improvements in strength, mobility, and performance of daily activities [7].

With the new presurgery immunotherapy treatment approach being implemented in Canada for individuals with melanoma, we now have more time to implement perioperative rehabilitation (rehabilitation around the surgical procedure) for this patient group. In individuals with other forms of cancer, prehabilitation, which is defined as a proactive approach to health care that involves enhancing a patient’s physical and psychological well-being before a surgical procedure [12], has been found to offer significant benefit by enhancing ROM, strength, physical function, and overall health prior to surgery or treatment [12-15]. By engaging in targeted rehabilitation before surgery, patients may improve their ROM, strength, endurance, and physical outcomes, leading to optimization of function and reduced treatment-related side effects after treatment [13-15]. Additionally, as we have demonstrated in our previous cancer rehabilitation research [16], rehabilitation before surgery can help optimize functional outcomes and alleviate anxiety and improve psychological well-being, empowering patients to approach their survivorships phases with confidence and resilience [17-19]. Despite growing evidence supporting rehabilitation interventions across multiple cancer populations, individuals with melanoma remain underrepresented in rehabilitation research.

Little evidence exists to guide rehabilitation delivery throughout prehabilitation and early postoperative phases in melanoma care, and no standardized rehabilitation models have been developed for patients undergoing this new treatment approach. Rehabilitation is not provided routinely for individuals with melanoma globally [20], and no form of perioperative rehabilitation services are available for most individuals with melanoma. Therefore, the purpose of this pilot trial is to determine the feasibility and preliminary effects of a rehabilitation strategy for individuals with melanoma before and after surgery within a cancer institution in Canada. The present intervention is informed by established principles in cancer rehabilitation [7,8] and prehabilitation [12,13] and was adapted from our previous cancer rehabilitation research demonstrating the feasibility and benefits of physiotherapy-led exercise and self-management interventions in oncology populations [16]. This was done because it targets impairments that are common across cancer populations, such as fatigue, physical deconditioning, and reduced functional capacity and quality of life. However, modifications were made to account for the unique treatment considerations experienced by individuals with melanoma, including timing of neoadjuvant immunotherapy, impairments related to wide local excision and node dissection, mobility concerns, and postoperative pain. The individualized approach used in the current intervention allows recommendations to be tailored according to treatment-related and melanoma-specific functional impairments. The selected feasibility outcomes will inform implementation of a future definitive trial specifically in those with melanoma, and the selected secondary outcomes reflect the hypothesized effects of the intervention.

### Research Questions and Hypotheses

This trial will answer 3 research questions.

First, is perioperative rehabilitation feasible for individuals diagnosed with melanoma requiring neoadjuvant immunotherapy and then receiving surgery? We hypothesize that the intervention will be feasible, as demonstrated by recruitment, retention, and adherence rates of >70% and high patient satisfaction with the intervention.

Second, do individuals with melanoma who participate in perioperative rehabilitation have improved outcomes (improved overall impairment score, physical activity level, functional mobility, ROM, grip strength, quality of life, perception of health status, and medication use) compared to those receiving usual care (no rehabilitation)? We hypothesize that those participating in the intervention will have improved overall impairment score, physical activity level, functional mobility, ROM, grip strength, quality of life, perception of health status, and medication use, compared to those receiving usual care.

Third, what is the frequency and nature of adverse events associated with perioperative rehabilitation for individuals with melanoma? We hypothesize that perioperative rehabilitation for individuals with melanoma will be safe and associated with few, if any, intervention-related adverse events.

## Methods

### Study Design

This is a pilot, parallel group randomized controlled trial (RCT). It will use a 1:1 allocation ratio, and participants will be randomly assigned to either the intervention or control group. Outcome assessments will be conducted at baseline and postintervention time points with assessors and data analysts blinded to group allocation. The protocol adheres to the SPIRIT (Standard Protocol Items: Recommendations for Interventional Trials) 2025 checklist [21] for protocols of randomized trials. Figure 1 shows the flow of participants across the study and associated analysis time points.

**Figure 1 figure1:**
[figure not shown]
Study flow.

### Ethical Considerations

This study was approved by the Hamilton Integrated Research Ethics Board (19542) and is registered on ClinicalTrials.gov (NCT07320222). All participants will complete written informed consent prior to taking part in the study. Participant privacy and confidentiality will be protected throughout the study, with outcome data being deidentified and no identifying information included in study reports. Study data will be stored securely and accessed only by authorized members of the research team. Participants will be reimbursed for parking expenses incurred while attending in-person intervention and assessment sessions. No additional compensation is provided.

### Participants and Recruitment

Eligible participants for this study include individuals who (1) have a diagnosis of melanoma, (2) are English-speaking, (3) are adults aged 18 years or older, and (4) are scheduled to undergo surgery at the Juravinski Cancer Centre in Hamilton, Ontario, after receiving a neoadjuvant immunotherapy regimen. Eligible potential participants will be referred to the study by their surgical oncologist or oncology care team using a consent to contact form, which includes the participants contact information and has the referring physician sign off that they are safe to exercise. Contact information of those who sign the consent to contact form will be given to the study research coordinator. They will be further screened for eligibility via their preferred method of communication by the research coordinator. Participants will be excluded if they (1) are aged <18 years, (2) are not undergoing neoadjuvant immunotherapy, and (3) self-report any chronic condition, cognitive impairment, or injury that would prevent them from participating independently in moderate intensity exercise.

### Sample Size

Based on sample size calculations for pilot data [22,23], we expect to recruit 30 participants for the study (15 in each group). For this project, the sample size was calculated based on the expected proportion of success of the primary feasibility outcome [23]. Using a Z value corresponding to a 95% CI (1.96), a desired margin of error (E) of 0.2, and an estimated population proportion of success (p) of 0.75 (based on expected estimated adherence rates), the calculated sample size for this pilot study was 18 participants (9 per group). With an expected dropout rate of up to 30% [24], the final sample size for this project was set at 30 participants (15 per group) to accommodate 1:1 block randomization and provide a conservative buffer.

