#### Control Group

The control group will receive usual care, which in the context of melanoma care at the Juravinski Cancer Centre includes no form of rehabilitation. Participants assigned to this group will not receive a rehabilitation referral from the study team; however, they are not limited from discussing rehabilitation options with their medical oncologist if they wish to learn more. Participants are not restricted from accessing rehabilitation services outside of the study.

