##### Adherence Rate

Adherence rate will be measured as adherence to the intervention session and is defined as the number of sessions attended.

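### The adherence sample size counts control participants, who have no sessions to attend; by the plan's own formula the planned 15 give about ±0.22, slightly short of the desired ±0.20

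*Protocol article*

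**What the plan says.** The Sample Size section gives every input of a single-proportion precision calculation. The confidence level is set by "Using a Z value corresponding to a 95% CI (1.96"), the precision by "a desired margin of error (E) of 0.2", and the proportion is "an estimated population proportion of success (p) of 0.75 (based on expected estimated adherence rates"). The stated result is that "the calculated sample size for this pilot study was 18 participants (9 per group"). The section then allows for loss ("With an expected dropout rate of up to 30" percent), and "the final sample size for this project was set at 30 participants (15 per group"), citing block randomization and a conservative buffer.

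The outcome that supplies the 0.75 is defined under Adherence Rate: "Adherence rate will be measured as adherence to the intervention session", counted as sessions attended. Table 2 judges it on the percentage of intervention sessions attended (go above 70%, amend from 50% to 70%, stop below 50%). Under Intervention Group, four sessions are offered to that arm. Under Control Group, usual care at this centre "includes no form of rehabilitation". Controls may seek rehabilitation elsewhere, but those are not study sessions.

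**The concern.** A one-proportion formula returns the number of people who must contribute a value to that proportion. Here the proportion is adherence to the study sessions, and a control participant cannot have one. Dividing the 18 between two arms leaves half of them contributing nothing to the estimate that produced the number. Raising the total to 30 enlarges the relevant arm to 15, which is still below 18.

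This is the only quantitative justification given for the sample size, and adherence is one of four progression criteria. A reader who takes the paragraph at face value would credit the adherence estimate with somewhat more precision than the stated calculation supports.

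**Working it through.** **Inputs (Sample Size section):** Z = 1.96, p = 0.75, E = 0.20, dropout up to 30%, final total 30 at 1:1. Sessions per intervention participant: 4 (Intervention Group). Study sessions per control: 0 (Control Group).

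**Step 1. Reproduce the plan's figure.**
n = Z² p(1 − p) / E² = 3.8416 × 0.1875 / 0.04 = 18.0075. The plan's 18 is confirmed (19 if rounded up strictly; the difference is immaterial). Dropout: 18 / 0.7 = 25.7, so 26, which the plan raises to 30.

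**Step 2. Count who contributes to adherence.** Of the calculated 18, the intervention arm holds 9. Of the final 30, it holds 15.

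**Step 3. Margin by the same formula,** half-width = 1.96 × √(0.1875 / n):

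| People with an adherence result | 95% half-width |
|---|---|
| 9 (intervention arm of the calculated 18) | 1.96 × √0.02083 = 0.283 |
| 15 (intervention arm of the final 30) | 1.96 × √0.01250 = 0.219 |
| 18 (if all contributed) | 1.96 × √0.01042 = 0.200 |

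**Step 4. Check with the Wilson interval at n = 15.**
Half-width = 1.96 × √(0.0125 + 3.8416 / (4 × 225)) / (1 + 3.8416 / 15) = 0.2538 / 1.2561 = 0.202. By this method the planned size almost meets the target.

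**Step 5. If adherence is a mean percentage of the four sessions.** The 15 people supply 15 × 4 = 60 session results. With within-person correlation ρ, the half-width is 1.96 × √(0.1875 × (1 + 3ρ) / 60). The document gives no ρ, so I assume the range 0 to 1:
- ρ = 0 gives 0.110.
- ρ = 1 gives 0.219.
- ±0.20 is met when 1 + 3ρ ≤ 0.04 × 60 / (3.8416 × 0.1875) = 3.33, that is, when ρ is at most about 0.78.

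On this definition ±0.22 is an upper limit.

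**Step 6. Retention, which uses both arms.** With n = 30 and p = 0.75, the half-width is 1.96 × √(0.1875 / 30) = 0.155. With p = 0.70, matching the plan's 30% dropout, it is 1.96 × √(0.21 / 30) = 0.164. About ±0.16 is a fair statement.

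**The case against.** **The trial enrols 15 per group, not 9.** This stands. The ±0.28 describes the calculated size before the dropout allowance, not the trial that will be run. At 15 the shortfall is about 0.02 by the plan's formula and 0.002 by Wilson.

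**Feasibility includes retention, for which both arms count.** True as far as it goes: 18 people would give ±0.20 for a proportion of 0.75, and the section speaks of the primary feasibility outcome in general. But it ties the 0.75 explicitly to adherence. If retention was meant, the stated basis is wrong and the paragraph still needs correcting.

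**Averaging four sessions per person may bring the margin under 0.20.** This also stands as a possibility. The Data Analysis Plan allows a mean or a frequency, and Table 2 can be read either way. It does not support the derivation as written, which treats adherence as one yes/no result per person. It does mean that ±0.22 should not be stated without saying which definition it belongs to.

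**The ±0.20 is only a desired margin.** Correct. Table 2 applies its thresholds to observed values, and feasibility is analysed descriptively, so no progression rule uses the margin.

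**Conclusion.** The point holds and is modest. The calculation is numerically right but applied to the wrong denominator: adherence can be observed in 9 of the calculated 18, or 15 of the 30 enrolled. By the plan's own formula these give ±0.28 and about ±0.22, against a desired ±0.20. The ±0.22 assumes true adherence of 0.75, one yes/no result per person and all 15 analysed.

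Two stronger readings are tempting, and the documents support neither.

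- **Only completers count.** A reader might take 30% off the 15, arrive at 10.5 people and a margin of 1.96 × √(0.1875 / 10.5) = ±0.26, and conclude that an observed 75% could not be separated from the stop zone below 50%. But adherence is defined by sessions attended, which is known for people who withdraw as well. The Data Analysis Plan specifies intention-to-treat, and nothing restricts adherence to completers.
- **The trial is too small.** A reader might infer that it must grow to 36 in total (2 × 18) before dropout. The plan presents ±0.20 as a wish, no decision depends on it, and the protocol already acknowledges under Strengths and Limitations that the sample is small. A gap of about 0.02 at the planned size does not call for more participants.

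**What to change.** This should be corrected in the Sample Size paragraph, leaving the total at 30:

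1. Remove the statement that 18 participants, split 9 per group, is the size that delivers ±0.20.
2. State that adherence is estimated in all 15 participants randomized to the intervention, with sessions missed after withdrawal counted as not attended.
3. Say whether adherence is one yes/no result per person or a mean percentage of the four sessions. Give the 95% margin at an expected 0.75 as about ±0.22 for the first, and at most that for the second.
4. State retention separately, on all 30, as about ±0.16.
5. Describe 30 as a pragmatic size.

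The cost is wording only. The stated precision for adherence becomes slightly less favourable; there are no extra participants and no added procedures.

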### Procedure

Once eligibility is confirmed, participants will complete a baseline assessment, after which they will be divided into 2 groups: intervention (CARE intervention) or control (usual care).

#### Intervention Group

The intervention group (CARE intervention) will include 4 perioperative intervention sessions led by a physiotherapist or kinesiologist trained in the treatment of individuals with cancer. The total intervention time will be approximately 4 months, with 2 of the intervention sessions occurring prior to surgery and 2 occurring after surgery. The intervention was designed to coincide with the immunotherapy treatment regime and key perioperative milestones [20]. The 2 preoperative sessions provide an opportunity for assessment, exercise education, prehabilitation, and development or an individualized exercise plan. They will be conducted in person whenever participants visit the cancer center for a scheduled appointment. The postoperative sessions support reassessment, progression of rehabilitation, management or postsurgical issues, and transition to long-term self-management. Participants will have the option of taking part in the postsurgery sessions in person or virtually. The approximately 4-month duration was selected to encompass the presurgical and early postsurgical recovery period while maintaining feasibility and minimizing participant burden in this pilot trial.

Each intervention session will include five components based on our previous research and guidelines for survivors of cancer: (1) review of current symptoms and function, (2) educational modules on exercise viewed on an iPad with the trainer, (3) tailored rehabilitation to maximize function, (4) home exercise program development or review, and (5) action plan development for participants to work on between sessions. Table 1 describes each intervention component. Figure 2 provides an overview of the CARE intervention components across the study period.

**Table 1 table1:** Components of the CARE intervention.

Component	Description
Review of current symptoms and function	Sessions 1-4 (items checked) Current symptoms (eg, pain, fatigue, range of motion, strength, balance scan) Posture Functional concerns (mobility observation) Vital signs (eg, heart rate, blood pressure, SpO2) Other changes since last visit
Education on exercise [16]	Session 1 Module 1: benefits of exercise, exercise safety, how to self-manage, how to set goals (15-minute video module) Module 2: posture, breathing techniques for stress and anxiety, managing energy levels, aerobic exercise description and parameters (15-minute video module) Session 2 Module 3: Strength training and parameters (15-minute video module) Module 4: Flexibility and alternative exercise types and parameters (15-minute video module) Session 3 Module 5: Self-monitoring activity level and function (15-minute video module) Module 6: Communicating about exercise, recovery after surgery (15-minute video module) Session 4 Module 7: How to progress and move forward with exercise, how to modify to meet needs (30-minute video module)
Tailored rehabilitation to maximize function	Sessions 1-4 (as needed by individual) Joint mobility to improve range of motion and muscle tension Postural awareness Balance Mobility
Home exercise program development/review^a^ [7]	Sessions 1-4 (following general exercise guidelines for cancer survivors [7,11]) Aerobic exercise (up to 150 minutes of moderate intensity aerobic exercise) Resistance training (twice weekly strength training for all major muscle groups) Flexibility exercises most days of the week for all major muscle groups
Action plan development [25]	Sessions 1-4: participants develop action plans related to exercise to work on between sessions. These include the following: Reflection of previous action plan success (if applicable) Current plan details (what, how, where, when, and how often) Rating of importance (0-10 scale) and confidence (0-10 scale) Potential barriers and how to adapt or modify the plan Potential supports Back-up plan Progress plan Commitment statement

^a^Trainers will tailor specific exercise program based on participant and cancer specific characteristics and work up to achieving these guidelines.

